## Abstract

**Background:**

Falls are a major public health concern with at least one third of people aged 65 years and over falling at least once per year, and half of these will fall repeatedly, which can lead to injury, pain, loss of function and independence, reduced quality of life and even death. Although the causes of falls are varied and complex, the age-related loss in muscle power has emerged as a useful predictor of disability and falls in older people. In this population, the requirements to produce explosive and rapid movements often occurs whilst simultaneously performing other attention-demanding cognitive or motor tasks, such as walking while talking or carrying an object. The primary aim of this study is to determine whether dual-task functional power training (DT-FPT) can reduce the rate of falls in community-dwelling older people.

**Methods/Design:**

The study design is an 18-month cluster randomised controlled trial in which 280 adults aged ≥65 years residing in retirement villages, who are at increased risk of falling, will be randomly allocated to: 1) an exercise programme involving DT-FPT, or 2) a usual care control group. The intervention is divided into 3 distinct phases: 6 months of supervised DT-FPT, a 6-month ‘step down’ maintenance programme, and a 6-month follow-up. The primary outcome will be the number of falls after 6, 12 and 18 months. Secondary outcomes will include: lower extremity muscle power and strength, grip strength, functional assessments of gait, reaction time and dynamic balance under single- and dual-task conditions, activities of daily living, quality of life, cognitive function and falls-related self-efficacy. We will also evaluate the cost-effectiveness of the programme for preventing falls.

**Discussion:**

The study offers a novel approach that may guide the development and implementation of future community-based falls prevention programmes that specifically focus on optimising muscle power and dual-task performance to reduce falls risk under ‘*real life*’ conditions in older adults. In addition, the ‘step down’ programme will provide new information about the efficacy of a less intensive maintenance programme for reducing the risk of falls over an extended period.

**Trial registration:**

Australian New Zealand Clinical Trials Registry: ACTRN12613001161718. Date registered 23 October 2013.

## Background

Falls in older adults are a common and major public health problem that can have serious consequences in terms of injury, pain, loss of function and independence, decreased quality of life and even death [1,2]. At least one third of community-dwelling people aged 65 and over fall at least once per year, and falls in these people are the leading cause of injury-related hospitalisation and death [3]. In Australia, it is projected that the total annual health cost attributable to fall-related injury will increase almost 3-fold to AUD$1.4 billion by 2051 [4]. Thus, there is a need to identify and implement cost-efficient and effective strategies to prevent falls in community-dwelling older adults to ensure that they live independently and relatively disease- and disability-free into old age.

It is well established that the causes of falling are varied and complex, but the age-related loss in muscle power has emerged as a major factor underlying impaired muscle function and disability in older people [5,6]. Muscle power reflects the ability of the muscle to produce force rapidly (that is, it is the product of force and velocity of contraction), and declines earlier and more rapidly with increasing age compared to muscle strength [7]. Many common daily functional tasks, such as the ability to get up from a chair, climb stairs and walk quickly to cross the road, are more strongly related to muscle power than muscle strength [8]. Indeed, the ability to recover from a loss of balance has been shown to be strongly related to the ability to step rapidly or grasp quickly for an object for support; factors associated with speed of generating force (power) [9]. The clinical relevance of this loss in muscle power has been demonstrated in a study that reported that older adults with low muscle power have a two- to three-fold greater risk of significant mobility impairment compared to individuals with low muscle strength [10]. There is also evidence that improvements in lower limb muscle power are more influential in producing clinically meaningful changes in muscle function than changes in muscle strength [11]. Thus, targeting deficits in lower extremity muscle power and movement velocity are likely to represent an effective strategy to optimise muscle function and reduce the risk of falls and related injuries in older people.

Extensive research into falls prevention has identified exercise to be an effective strategy to counteract key risk factors for falls, such as muscle weakness and poor balance, and reduce the risk of falling in older people. However, a recent meta-analysis of randomised controlled trials reported that exercise only reduced the risk of falling by an average of 16%, and that not all modes of exercise were equally effective with those studies that included walking being less effective [12]. While walking is a popular activity for many older adults and can substantially lower the risk of many chronic diseases, a large proportion of falls occur during walking [13]. Thus, there is a need to explore other novel exercise interventions that can improve multiple risk factors for falls (gait, balance, reaction time) and lower fall rates more effectively. Progressive resistance training (PRT) is one approach that is often recommended because of its reported benefits on muscle strength, but there are mixed findings with regard to the efficacy of this mode of training for preventing falls [12,14]. This is perhaps not surprising given the concept of training specificity. Most PRT programmes encourage slow velocity contractions (2 to 4 seconds concentric phase) at a moderate to high percentage of maximal force (approximately 60 to 80% of 1-repetition maximum strength (1-RM)). However, many common tasks related to mobility and daily perturbations require rapid coordinated and dynamic contractions within 50 to 200 ms, which is considerably less than the time needed to achieve maximal muscle force (approximately 400 to 600 ms) [15]. Thus, strategies that aim to enhance the ability to generate force quickly, and that are specific to tasks of daily living, are likely to be more relevant to the maintenance of muscle function and thereby prevent falls in older adults.

In recent years there has been interest in the role of high-velocity (HV) PRT, or power training, as a novel form of training to enhance muscle power and function in older adults. This mode of training is characterised by rapid concentric movements followed by a slower eccentric phase performed at moderate to high loads. In healthy young and older adults, a number of intervention trials have shown that HV-PRT using exercise machines conducted within a controlled setting was effective for improving muscle strength, power and functional performance [16-23]. The findings from a meta-analysis of the limited trials available also revealed that the functional gains following HV-PRT were greater than those that can be achieved through traditional PRT [24]. Most of the previous studies involving HV-PRT have used specialised exercise equipment within a controlled setting, which may not be readily accessible to many community-dwelling older adults. Importantly for older people, high-load or high-intensity training is not required as several studies have shown that training at low load and high velocity leads to similar (or even greater) gains in balance, movement speed and muscle strength compared to traditional slow speed PRT [23,25,26]. There is also evidence that dynamic functional exercises (stair climbing, chair stands, step-ups) performed rapidly and made progressively more challenging through the use of weighted vests or elastic bands/tubing can significantly improve muscle power and function [16,27]. However, a limitation of nearly all these studies is that they included small sample sizes and were performed in a controlled setting. To our knowledge, this will be the first community-based, randomised controlled trial to evaluate the long-term effects of HV-PRT on falls in older people.

For many older adults, the risk of falls is increased when they are required to undertake a secondary or concurrent cognitive or motor task (referred to as the ‘dual-task paradigm’), such as walking while talking, carrying objects or watching traffic [13,28,29]. Previous research has shown that cognitive deficits in older people, particularly deficits in executive function such as the ability to concentrate, to attend selectively, multi-task and to plan and strategise [30], are associated with both risk factors for falls (for example, postural instability, impaired gait, reduced ability to perform activities of daily living (ADL)); and future falls [31,32]. Indeed, there is evidence that under dual-task conditions, older adults exhibit poorer reaction times, reduced walking speed, increased sway, more frequent contact with obstacles whilst walking and slower step velocities, compared to single-task conditions [33-37]. Difficulties in dual-task conditions have also been associated with a history of falls and risk of future falls in community-dwelling older adults [31,37]. Several short-term trials and pilot studies in healthy older adults and those with stroke, Parkinson’s disease and dementia, have shown that balance or stepping programmes incorporating dual-tasking, such as exercising whilst performing a cognitive and/or motor task, were effective for improving balance and gait under dual-task conditions [38-45]. In contrast, single-task training was not transferable to balance performance under dual-task conditions [40]. This highlights the need for targeted falls prevention programmes that incorporate the principle of training specificity and replicate ‘real-life’ everyday situations in terms of how and where falls are likely to occur. To our knowledge, this study will be the first to investigate whether dual-task functional power training can reduce the rate of falls and improve risk factors for falls under single and dual-task conditions in older people at risk of falling. Furthermore, previous research has consistently shown that many of the benefits of exercise for falls prevention are lost following the cessation of supervised or intensive programmes [46,47]. Thus, there is a need to identify safe and effective strategies to maintain any initial benefits derived from structured or intensive programmes. In this study, we will examine the efficacy of a less intensive ‘step down’ maintenance programme on fall rates after an initial intensive 6-month structured training programme. We will also examine the cost-effectiveness of the intervention and maintenance programme for preventing falls in older community-dwellers.

The primary aim of this community-based, cluster randomised controlled trial is to evaluate whether dual-task functional power training (DT-FPT) can reduce the rate of falls in community-dwelling older adults at increased risk of falling. Secondary aims of the study are to:Determine if DT-FPT can improve lower extremity muscle power, balance and gait under single and dual-task simulated ‘*real-life’* conditions.Evaluate the effects of DT-FPT on health-related quality of life (HR-QoL), falls-related self-efficacy and cognitive function.Evaluate the efficacy of a ‘step down’ maintenance programme on falls risk.Determine the cost-effectiveness of DT-FPT and the ‘step down’ maintenance programme for preventing falls. The results will be expressed as the incremental cost of the intervention in monetary terms per unit gain per fall averted.

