## Methods/Design

### Study design

This is an 18-month, community-based, cluster randomised controlled trial in which older adults residing in retirement villages, who are at increased risk of falling, will be randomly allocated to: 1) an exercise programme involving dual-task functional power training (DT-FPT), or 2) a usual care control group. The intervention is divided into 3 distinct phases: 6 months of supervised and structured DT-FPT, a 6-month ‘step down’ maintenance programme, and a 6-month follow-up. Multi-care level retirement villages will be recruited but only people that live independently in apartments or units, but share common-room facilities, will be recruited. The trial is managed by the Centre for Physical Activity and Nutrition Research at Deakin University, Burwood, Melbourne, Australia and is funded by a National Health and Medical Research Council (NHMRC) Project Grant (ID1046267). The study has been approved by the Deakin University Human Research Ethics Committee (HREC 2013-051), and is registered with the Australian and New Zealand Clinical Trials Registry (ACTRN12613001161718). Written informed consent will be obtained from all participants prior to commencement of the trial.

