#### Randomisation

Randomisation will be performed by cluster (village) to avoid any potential contamination and facilitate logistical arrangement. Each village will be given an ID number and group assignment by blocks of 2, stratified by village size (<75 or ≥ 75 residents), will be performed by a researcher not involved in the study using computer-generated random numbers (Microsoft Excel, Microsoft Corp., Redmond, WA, USA). A flow diagram of the study protocol is outlined in Figure 1.

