#### ‘Step down’ maintenance programme and follow-up

A 6-month ‘step down’ maintenance programme will be introduced after the supervised training for the intervention group since previous trials have shown that the benefits of exercise on falls incidence are largely lost after programme cessation [46,47]. The ‘step down’ represents a decrease in the level of free supervised training that will be offered to the participants by the exercise staff who delivered the first 6-months of the programme. Prior to this phase we will liaise with all village managers to discuss strategies as to how they can continue to offer the programme within their village without the intensive intervention of the research staff. Village managers will be provided with a number of potential options as to how they can continue to offer the programme to the residents. To facilitate this transition, participants will be offered 1 weekly 1-hour exercise class led by our trained exercise staff who have completed our ‘train-the-trainers’ workshop. In addition, since one of the goals of the main intervention is to improve gait and muscle function under dual-task conditions, participants will also be encouraged to undertake at least one brisk walking session per week. Within each village, staff/participants will be encouraged to form walking groups. Compliance with the ‘step down’ programme will be monitored by attendance sheets completed by the staff at each village and a diary for recording the walking. After the 6-month ‘step down’ programme, participants will be followed for a further 6 months to establish the long-term residual effects on falls. Participants and staff at the villages will not receive any support or advice during this final 6-month follow-up.

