#### Cost-effectiveness analysis (CEA)

The CEA will be used to determine the monetary treatment costs of implementing the exercise programme and cost of outcomes (for example, falls and their consequences). The results will provide an incremental cost per fall averted for the DT-FPT and ‘step down’ programme. The incremental cost-effectiveness ratio (ICER) is the ratio of the incremental difference in treatment cost to the cost-saving (fewer falls). The ICER will be used in future decision-making on the allocation of resources, which maximises the health effects for a given amount of resources. The following measures will be collected: 1) the costs of implementing the programme (for example, staff costs, training, vehicle costs, capital costs and consumables), and 2) costs of health services (for example, directly related to a fall including inpatient hospital admissions, emergency department presentations and other health and community service contact) derived from the monthly calendars. The results will be expressed as the incremental cost (dollars) per fall averted among those randomised to the DT-FPT and ‘step down’ programme versus usual care. Research-related costs will not be included in the CEA.

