## Discussion

Many falls in older people result from an inability to generate sufficient lower limb muscle power to produce an explosive and rapid movement to step quickly when balance is lost. This is confounded further when simultaneously performing concurrent attention-demanding tasks (‘dual-task’ paradigm), such as talking while walking or negotiating traffic or obstacles. Despite the clinical relevance of muscle power and dual-tasking to ‘*real life*’ situations*,* no studies have examined the efficacy of either approach for preventing falls in a large-scale randomised controlled trial. We expect that the results from this trial will guide the development and implementation of future community-based falls prevention programmes that specifically focus on optimising muscle power and function and reducing falls risk under ‘*real-life’* conditions in older adults at risk of falling. If successful, the pragmatic design of the exercise intervention programme could be easily adopted to routine practice. The successful delivery of the intervention within retirement villages is also critical as it overcomes common barriers to exercise participation for older people. Furthermore, the ‘step down’ programme will provide important new information about the efficacy of a less intensive maintenance programme for reducing the risk of falls over an extended period in community-dwelling older adults.

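### The design can estimate falls under supervised training followed by step-down versus usual care, but not the efficacy of the step-down itself, which is a stated secondary aim

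*Protocol article*

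**What the plan says.** The list of secondary aims at the end of the Background includes, as an item of its own, to "Evaluate the efficacy of a ‘step down’ maintenance programme on falls risk". The paragraph before that list, the Discussion part of the abstract and the main Discussion repeat the promise. The main Discussion says that the step-down "programme will provide important new information about the efficacy of a less intensive maintenance programme for reducing the risk of falls over an extended period".

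The design is set out in full:

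- **Arms** (Study design): participants are "randomly allocated to: 1) an exercise programme involving dual-task functional power training (DT-FPT), or 2) a usual care control group".
- **Sequence in the intervention arm** (Study design): "6 months of supervised and structured DT-FPT, a 6-month ‘step down’ maintenance programme, and a 6-month follow-up".
- **Who receives the step-down** (section on the step-down programme and follow-up): "A 6-month ‘step down’ maintenance programme will be introduced after the supervised training for the intervention group". In the final 6 months, support is withdrawn.
- **Allocation** (Randomisation): "Randomisation will be performed by cluster (village) to avoid any potential contamination". No second randomisation is described.
- **Analysis** (Statistical methods): the two randomised groups are compared at each follow-up.
- **Cost-effectiveness** (CEA section): "The results will provide an incremental cost per fall averted for the DT-FPT and ‘step down’ programme". The same section then defines the contrast as those randomised to the combined programme versus usual care.

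**The concern.** Efficacy of a maintenance programme means its effect compared with not having it. After a supervised phase, the natural comparator is a group that had the same supervised phase and then stopped. This trial has no such group. A between-group difference in months 7 to 12 could come from the weekly class and the walking, from benefit left over from the first 6 months, or from both.

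The stake is what the trial may conclude. If the aim stands as worded, a persisting difference invites the reading that the step-down works, even when the step-down adds nothing. The primary aim is not affected.

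**Working it through.** **1. What is randomised in each period**

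| Period | Intervention villages | Control villages | What the contrast estimates |
|---|---|---|---|
| Months 0 to 6 | Supervised DT-FPT | Usual care | Effect of supervised DT-FPT, S |
| Months 7 to 12 | Step-down, after DT-FPT | Usual care | Carry-over C plus step-down effect D |
| Months 13 to 18 | No support, after both | Usual care | Residual effect of the whole sequence, R |

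**2. Identifiability**

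Over the first two periods there are 2 arms × 2 periods = 4 cell means. The parameters are two period levels, S, C and D, which makes 5. C and D enter only the intervention cell of months 7 to 12, and only as C + D. The design matrix therefore has rank 4 for 5 parameters, and C + D is estimable while D alone is not. Counting and testing months 7 to 12 separately does not change this. One added cell, intervention villages that stop at month 6, would supply C alone and bring the rank to 5 of 5.

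Adding months 13 to 18 gives 6 cell means but also two new parameters, a third period level and R, so there are 7 parameters and the rank is 6. R is what is left of both phases after support ends. Comparing C + D with R does not isolate D, because carry-over from the supervised phase may fade over the same interval.

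**3. Illustration of size**

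The documents give no rate of decay, so the values here are assumptions:

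- The rate ratio at month 6 is 0.6. The number is borrowed from the Sample size section, where 45% versus 27% gives 1 − 27/45 = 0.40. There it is a drop in the proportion of participants who fall during the study. Using it as a month-6 rate ratio is my assumption, not the plan's.
- The step-down has no effect, so D = 0.
- The log rate ratio decays with half-life h months: log RR(t) = ln(0.6) × 2^(−t/h), with t in months after the supervised phase.

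The mean over t = 0 to 6 is ln(0.6) × [h / (6 ln 2)] × (1 − 2^(−6/h)), where ln(0.6) = −0.511.

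| h (months) | Averaging factor | Mean log RR | Mean RR | Apparent reduction |
|---|---|---|---|---|
| 1 | 0.237 | −0.121 | 0.89 | 11% |
| 3 | 0.541 | −0.276 | 0.76 | 24% |
| 6 | 0.721 | −0.368 | 0.69 | 31% |

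In each row the step-down does nothing, yet months 7 to 12 show a benefit over usual care.

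**The case against.** **The aim may only mean persistence.** The Background speaks of maintaining initial benefits after the intensive programme, and Study design presents the step-down as one phase of a single intervention. On that reading the aim asks whether the between-group difference lasts, and the planned comparison answers it. It stands that the planned analysis needs no change. It does not stand that the aim says this: the aim names the efficacy of the step-down programme, and the abstract and Discussion repeat that.

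**Earlier trials show that benefit is largely lost after stopping.** The step-down section cites this as its reason for the phase. Set against it, a persisting difference could be credited to the step-down. That is a historical comparison with other programmes, and largely lost does not mean lost at once or completely. The same section plans to study residual effects after month 12, so it allows that effects can outlast a programme.

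**Withdrawal at month 12 offers another comparison.** The between-group difference can be compared before and after withdrawal, with concurrent controls for time trend. This is informative, but it remains confounded with fading carry-over.

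**Cost-effectiveness.** A reader might infer that the cost-effectiveness aim is also unanswerable. The documents do not support that. The CEA section defines the ratio for those randomised to the combined programme versus usual care, which the design can estimate, and no separate step-down ratio is planned. Only the step-down's own cost per fall averted, relative to stopping at month 6, would be out of reach.

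**Misattribution.** A reader might also infer that the trial plans to credit the whole months 7 to 12 difference to the step-down. Nothing in the article commits to that. The wording of the aim permits it, which is a narrower criticism.

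**Conclusion.** The point holds for the efficacy aim. With two arms, one randomisation and the step-down given to the whole intervention group, months 7 to 12 identify only carry-over plus step-down. This follows from the design and needs no assumed numbers. An analysis plan cannot supply the missing comparator, so the matter is not one that the article could have left to another document.

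The 11% to 31% range is illustrative. It rests on a month-6 rate ratio of 0.6, a step-down with no effect and half-lives chosen here. It is not a forecast of bias, and the Sample size section does not state a month-6 rate ratio.

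The primary aim, the planned group comparisons and the package cost-effectiveness ratio are sound on this point. What needs correcting is a prominent secondary claim that goes beyond what the design can show.

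**What to change.** - **Aim.** Reword the secondary aim along these lines: *evaluate falls in months 7 to 12, and to month 18, under supervised DT-FPT followed by the step-down programme, compared with usual care.*
- **Consistency.** Align the abstract, the last paragraph of the Background before the aims, and the Discussion.
- **Limit.** State that the effect of the step-down beyond carry-over from the supervised phase is not identified by this design.
- **Cost-effectiveness.** Keep one incremental cost per fall averted for the combined programme versus usual care, over the full 18 months for which falls are recorded, and claim no separate step-down ratio. Cutting the ratio off at month 12 would discard later falls and fall-related costs in both arms.

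This costs wording only: no new data, participants or analyses. The trial gives up a separate step-down efficacy claim.

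Randomising intervention villages at month 6 to step-down or stopping would identify the effect, but not at this size. Of about 15 villages, 7 or 8 are in the intervention arm. Splitting 140 participants gives 70 per half, and 15% loss with the plan's design effect leaves 70 × 0.85 / 1.19 = 50 effective participants. If 45% fell after stopping and 27% under step-down (assumed), power would be about 0.47; for 36% versus 27% (assumed), about 0.16. Rewording is the proportionate change.
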